## Abstract

**Background:**

Adolescents in low- and middle-income countries in need of mental health care often do not receive it due to stigma, cost, and lack of mental health professionals. Culturally appropriate, brief, and low-cost interventions delivered by lay-providers can help overcome these barriers and appear effective at reducing symptoms of depression and anxiety until several months post-intervention. However, little is known about whether these interventions may have long-term effects on health, mental health, social, or academic outcomes.

**Methods:**

Three previous randomized controlled trials of the Shamiri intervention, a 4-week, group-delivered, lay-provider-led intervention, have been conducted in Kenyan high schools. Shamiri teaches positively focused intervention elements (i.e., growth mindset and strategies for growth, gratitude, and value affirmation) to target symptoms of depression and anxiety and to improve academic performance and social relationships, by fostering character strengths. In this long-term follow-up study, we will test whether these mental health, academic, social, and character-strength outcomes, along with related health outcomes (e.g., sleep quality, heart-rate variability and activity level measured via wearables, HIV risk behaviors, alcohol and substance use), differ between the intervention and control group at 3–4-year follow-up. For primary analyses (*N*_anticipated_ = 432), youths who participated in the three previous trials will be contacted again to assess whether outcomes at 3–4-year-follow-up differ for those in the Shamiri Intervention group compared to those in the study-skills active control group. Multi-level models will be used to model trajectories over time of primary outcomes and secondary outcomes that were collected in previous trials. For outcomes only collected at 3–4-year follow-up, tests of location difference (e.g., *t*-tests) will be used to assess group differences in metric outcomes and difference tests (e.g., odds ratios) will be used to assess differences in categorical outcomes. Finally, standardized effect sizes will be used to compare groups on all measures.

**Discussion:**

This follow-up study of participants from three randomized controlled trials of the Shamiri intervention will provide evidence bearing on the long-term and health and mental health effects of brief, lay-provider-delivered character strength interventions for youth in low- and middle-income countries.

**Trial registration:**

PACTR Trial ID: PACTR202201600200783. Approved on January 21, 2022.

**Supplementary Information:**

The online version contains supplementary material available at 10.1186/s13063-022-06394-7.

## Administrative information

Note: the numbers in curly brackets in this protocol refer to SPIRIT checklist item numbers. The order of the items has been modified to group similar items (see http://www.equator-network.org/reporting-guidelines/spirit-2013-statement-defining-standard-protocol-items-for-clinical-trials/).

## Introduction

### Background and rationale {6a}

Recently, there has been increasing recognition of mental health as an essential component of health, with the World Health Organization (WHO) declaring that health cannot exist without mental health [1]. Reports of mental health issues among children and adolescents are increasing globally, especially due to the COVID-19 pandemic [2], with around 20% of children and adolescents having a mental health condition, and most mental health disorders originating between the ages of 12 and 24 [3, 4]. Poor mental health is associated with many additional concerns for health and development among young people, including lower educational achievement, substance use problems, risk of experiencing and perpetrating violence, relationship problems, poor reproductive and sexual health, and suicide risk [4–8].

School-going adolescents in many parts of the world, particularly in low-and middle-income countries (LMICs) such as those in sub-Saharan Africa (SSA), are in urgent need of innovative ways to address mental health burdens, as they face several barriers to accessing care. Such barriers include a dearth of trained mental health clinicians and stigma associated with mental health conditions and care [9, 10]. Additionally, the duration and cost of most mental health treatments—many of which were not designed for use in SSA [11]—are prohibitive to many youths and families [4, 12].

These barriers to care have led researchers to test low-cost, low-stigma, and scalable mental health solutions in SSA, some of which could be considered character strength interventions (i.e., interventions to build character strengths and apply them to one’s life) [13] and wise interventions (i.e., brief, precise interventions targeting specific psychological processes that influence meaning-making about the self and the world) [14]. One intervention drawing from this literature, Shamiri, meaning “Thrive” in Kiswahili, is delivered in a group setting by near-peer high school graduate lay-providers, and is designed to change the way high-school-aged youths view themselves and the world [15, 16]. Shamiri takes four hours to implement over the course of four weeks, and has three components: growth mindset [17] and strategies for growth, gratitude [18], and value affirmation [19].

Previous research on Shamiri in Kenya has shown promising improvements in youth mental health, psychosocial, and academic outcomes at post-intervention and seven-months follow-up [17, 20]. In a randomized controlled trial (RCT) of Shamiri with 51 Kenyan adolescents with clinically elevated depression and/or anxiety symptoms, we found improvements in depression and anxiety symptoms, academic performance, and perceived social support from friends when compared to an active study skills control group immediately post-intervention [15]. In a well-powered (*N* = 413), preregistered replication of this study [16], youths in the Shamiri intervention exhibited improvements in depression and anxiety symptoms over time, and when compared to the active study skills control group. These improvements were maintained at 7 months post-intervention [20]. This study also indicated that Shamiri is feasible and acceptable to Kenyan youths. A third ongoing trial is intended to investigate the effects of each of the three components of the Shamiri intervention against the full Shamiri protocol and an active study skills control group [21].

Our previous work which focused on developing and testing Shamiri suggests that this short character strength intervention has the potential to improve social, academic, and mental health outcomes of youth in Kenya. An important next step is to evaluate Shamiri’s potential for improving these and other related health outcomes in the long-term. Therefore, in this proposed study, we will investigate the Shamiri intervention’s effects, relative to the active control condition’s effects, on a wider variety of health, wellbeing, and social outcomes at 3–4-year follow-up of participants in our three prior RCTs. To the best of our knowledge, this will be the first study to test the effects of character strength interventions on such a rich range of health outcomes over such an extended period.

### Objectives {7}

This study has four goals. Our primary goal is to compare the effects of the Shamiri intervention and control condition on the primary outcomes (depressive symptoms, anxiety symptoms, academic performance, and social support) in the long-term. We hypothesize that the intervention group will outperform the active control on each of our primary outcomes. Secondarily, we aim to compare the effects of each group on secondary outcomes (described below in {12}). We also aim to explore for whom these interventions are most effective in the long-term. Finally, in an exploratory fashion, we wish to compare effects for the intervention groups that received a single component of the Shamiri intervention against the group that received the full Shamiri intervention and the active control group.

### Trial design {8}

This study is a parallel-group randomized comparative effectiveness trial with five arms: (1) the Combined Shamiri Intervention (consisting of a growth element, a gratitude element, and a value affirmation element), (2) the Growth Intervention, which encompasses content related to growth mindset and strategies for growth, (3) the Gratitude Intervention, which incorporates content to build feelings of gratitude and expression of gratitude, (4) the Values Intervention, which incorporates content to help students identify, affirm, and better act on their personal values and sense of purpose, and (5) a Study Skills Control, an active control group teaching students study skills that may be useful to them as students. Each condition is described further in section {11a}. All participants in this trial have already completed intervention in these conditions in three previous RCTs. The first and second RCT had two conditions, the Combined Shamiri Intervention, and the Study Skills control, and these interventions were administered with a 1:1 ratio, or equal probability for assignment to each of the two conditions. In the third RCT, participants were allocated within each school to the five conditions with a 1:1:1:1:1 ratio or equal probability for assignment to each of the five conditions. Each arm required 4-h-long sessions spanning 4 weeks and was delivered in a group of 8–15 students by a local lay provider, aged between 18 and 24. Measures of mental health, wellbeing, and character strengths were collected in the three previous RCTs at baseline, 2-week midpoint, 4-week endpoint, and 1-month, 3-month, 7-month, and 9-month follow-up. For this long-term follow-up, measures of mental health, wellbeing, character strengths, stress, health behaviors, socioeconomic and health status will be collected at 3–4 years follow-up. Academic data was collected in the three previous RCTs for the school terms before, during, and immediately after the intervention. For the current trial, academic data will be collected for the last year of secondary school. De-identified trial data will be available upon request.

## Methods: participants, interventions, and outcomes

### Study setting {9}

This study will be conducted with participants who attended secondary school in Kiambu and Nairobi counties in Kenya. For participants under 18 or still in school, we will visit their schools to conduct data collection. Data collection for adults no longer in school will take place in the Nairobi area at the African Mental Health Research and Training Foundation (AMHRTF) offices. Adult participants will present themselves to AMHRTF for self-reports and assessment by a clinician. These participants will also visit Kenyatta National Hospital’s Voluntary Counselling & Testing Centre if they wish to know their HIV status.

### Eligibility criteria {10}

All participants who have taken part in three previous RCTs [15, 20, 21] of the in-person, group-based, 4-week Shamiri intervention, and had elevated symptoms of depression or anxiety at baseline of the previous RCTs (defined as scores of 10 or over on the Generalized Anxiety Disorder-7 (GAD) and 15 or over on the Patient Health Questionnaire-8 (PHQ-8)) are eligible for enrolment in this long-term follow-up study. Participant consent or assent, and in the case of minors, guardian consent, will also be required for participation. No additional exclusion criteria will be applied.

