#### Sample size {14}

Combining the three RCTs from which participants will be recruited, our expected sample size will come to ~ 720 youths with elevated symptoms of anxiety or depression at baseline (see inclusion criteria). However, since this is a long-term follow up study, based on our previous experience working in this setting [20], we believe that we will have an attrition rate of ~ 40%. As such, our target sample size for main analyses in this follow-up study is expected to be 432 participants. Of note, this sample size leaves us sufficiently powered: for the most complex planned analyses (multi-level models with four repeated measures), we could detect a small-medium effect size [28] with a power of .8 and a p-value (alpha level) of .05 [67].

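### The inclusion rule joins its two baseline cut-offs with *and*, although the criterion it defines and the pool of about 720 are both described with *or*

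*Protocol article*

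**What the plan says.** Eligibility criteria {10} opens eligibility to participants of the three earlier trials who "had elevated symptoms of depression or anxiety at baseline of the previous RCTs". In the same sentence a parenthesis turns this into numbers: "defined as scores of 10 or over on the Generalized Anxiety Disorder-7 (GAD) and 15 or over on the Patient Health Questionnaire-8 (PHQ-8". Apart from consent or assent, nothing further is required, and the section adds no exclusion criteria. No other section states the cut-offs.

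Sample size {14} puts the combined pool at about "720 youths with elevated symptoms of anxiety or depression at baseline (see inclusion criteria", so it uses *or* and refers the reader back to {10}. It then assumes about 40% attrition and concludes that "our target sample size for main analyses in this follow-up study is expected to be 432 participants". A small-to-medium effect, with no number attached, is said to be detectable "with a power of .8 and a p-value (alpha level) of .05".

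Background and rationale {6a} describes the sample of the first source trial as "51 Kenyan adolescents with clinically elevated depression and/or anxiety symptoms".

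**The concern.** The sentence in {10} names one population and defines another. Raised depression *or* anxiety is everyone over at least one cut-off. GAD-7 of 10 or over *and* PHQ-8 of 15 or over is, taken literally, only those over both. Whoever turns the sentence into a filter on the stored baseline scores must choose between the two, and the parenthesis, which is the only part with numbers in it, says *and*.

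Two things depend on the choice. One is who is traced and analysed: on the literal reading, youths raised on a single scale drop out, and the results describe only youths raised on both. The other is the sample size, because the 720 is described on the *or* reading yet rests by cross-reference on a rule that says *and*.

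**Working it through.** **Passages side by side**

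| Place | Connector |
|---|---|
| {10}, main clause | *or* |
| {10}, defining parenthesis | *and* |
| {14}, description of the 720 | *or*, with a reference back to {10} |
| {6a}, first source trial | *and/or* |

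Three of the four statements agree on the union. The one that differs is the one that carries the cut-offs. No section says that both cut-offs must be met.

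**The plan's own figure**

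Inputs from {14}: pool about 720, attrition about 40%.

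N followed up = 720 × (1 − 0.40) = 432. This reproduces the stated target exactly.

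The power statement cannot be reproduced, because the article gives no numerical effect size, intraclass correlation or sidedness. For reference only, take the normal approximation for two means: two-sided alpha 0.05, power 0.80, one time point, no clustering, all 432 split 1:1.

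d = (1.960 + 0.842) × √(4/432) = 0.27

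**The literal reading**

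Let f be the share of the *or* pool that meets both cut-offs. Then eligible = 720 × f and followed up = 720 × f × 0.60. Youths meeting both are a subset of those meeting either, so f cannot exceed 1 and is below 1 unless every youth meets both. The documents do not give f. The values below are assumptions that show how the result depends on it, using the same reference approximation.

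| Assumed f | Eligible | After 40% attrition | Detectable d | Power at d = 0.27 |
|---|---|---|---|---|
| 1 (*or* reading) | 720 | 432 | 0.27 | 0.80 |
| 0.8 | 576 | 346 | 0.30 | 0.71 |
| 0.5 | 360 | 216 | 0.38 | 0.51 |
| 0.3 | 216 | 130 | 0.49 | 0.34 |
| 0.2 | 144 | 86 | 0.60 | 0.24 |

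The direction is certain. The size is not, and none of the rows below the first is a documented figure.

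**The case against.** The strongest reply is that *and* simply lists one cut-off per scale: anxiety is GAD-7 of 10 or over, depression is PHQ-8 of 15 or over, and the main clause says that either suffices. This is a natural reading and probably the intended one. {14} and {6a} support it, and on that reading 720 and 432 stand unchanged. All of this is accepted. What remains is that the reader must go to other sections to settle what the only numeric inclusion rule means.

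Three stronger readings are tempting, and the documents do not carry them:

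- **That the sample is much smaller than planned.** A reader might infer this by modelling the overlap. For example, assume a bivariate-normal model with GAD-7 of 10 or over in 30–60%, PHQ-8 of 15 or over in 10–30%, and correlation 0.5–0.7. Then f is about 0.15–0.47, giving roughly 106–341 eligible and 64–205 after attrition. Every one of those inputs is assumed. The protocol gives no prevalence, correlation or overlap. The planned analysis is also a clustered repeated-measures model, so the simple detectable effects above are only a guide.
- **That the 720 or the power is wrong.** The 720 is described with *or*, and the arithmetic from it is exact. Nothing shows that it was counted any other way.
- **That the three cohorts will be selected inconsistently.** Table 1 places the eligibility screen in the source trials, Recruitment {15} has school staff trace earlier participants, and one steering committee oversees recruitment and data. No section has sites applying the cut-offs.

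**Conclusion.** The point holds as a contradiction in a stated eligibility threshold. {10} describes the population with *or* and defines it with *and*, and {14} counts with *or* while citing {10}. Read literally, the definition admits only a subset of the pool behind the 720 and the 432, smaller by an amount the protocol does not give. The balance of the text favours *or*, and on that reading the planned numbers are unaffected. This is therefore an inclusion rule that should be corrected before it is used as a filter. It is not a demonstrated error in sample size or power. The conclusion rests on the wording alone and needs none of the assumed overlaps.

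**What to change.** Reconcile {10} and {14}.

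- **If *or* is intended**, as {6a} and {14} indicate: reword the parenthesis in {10} to a GAD-7 score of 10 or over or a PHQ-8 score of 15 or over (or both) at baseline of the source trial. Apply that one rule to all three source databases and confirm that the figure of about 720 was counted this way.
- **If both cut-offs were meant to be required**: change the main clause of {10} and the description in {14} to match, and restate the 720, the 432 and the detectable effect from the actual count.

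The cost in the first case is one word and a recount from baseline scores already held. The second case also needs a revised sample-size paragraph. Neither requires new data.

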### Who will take informed consent? {26a}

A member of the study team who is from and living in Kenya will seek informed consent and assent prior to collecting follow-up measures. We will provide participants with a digital consent form (see supplementary materials for the model consent form to be used). Then, a member of the study team with appropriate ethical training and Institutional Review Board (IRB) approval will walk the participants through the consent form and clarify any questions they may have. They will emphasize the voluntary nature of participation in the study.

While we hope to seek permission/consent from parents of minors who wish to participate in our study, following local customs of boarding schools in Kenya, where students do not have direct access to their parents, as well as the logistical difficulty in obtaining written consent from parents disbursed throughout the country with limited access to timely postal communication, we will work with the school administration to obtain consent from the parents of minors. Specifically, we will work with school administrators to obtain informed consent on behalf of parents using the customary methods of the school (i.e., sending text messages or calling parents). The participants who are minors will also be asked to provide informed assent on site.

### Additional consent provisions for collection and use of participant data and biological specimens {26b}

We will seek additional consent prior to taking physical measures of health from participants. They will be informed that these measures are voluntary and that they may opt out of them at any time as they wish. We will also seek additional consent from participants over 18 years old who are not in school and wish to attend Kenyatta National Hospital’s Voluntary Counselling & Testing Center for an HIV test and inform participants that if they wish to be tested for HIV, we will pay for the test, and if they wish, they may report the result of the test back to the study team, but that they are not required to do so.

This trial does not involve collection, storage, or analysis of biological specimens.

### Interventions

#### Explanation for the choice of comparators {6b}

For primary analyses, the Shamiri intervention will be compared to a Study Skills active control condition of equal duration and highly similar format. As detailed further in a protocol for one of the three RCTs [21] from which participants will be drawn for this study, the Study Skills active control condition was selected as a comparator for several reasons. First, active control conditions typically provide a more robust comparison than no-treatment or waitlist control conditions [22]. Second, because students in Kenyan high schools report pressure to succeed academically at high rate and severity [23], improving study skills may be practically useful and may help reduce stress and anxiety for students. Third, past research has shown that symptoms of mental health problems may indeed be somewhat alleviated by the Study Skills control condition [15]. Finally, those in the Study Skills control condition participated in weekly small group sessions led by a lay-provider; this regular contact may have helped lower barriers to requesting needed support from a lay-provider.

#### Intervention description {11a}

Participants in three RCTs have previously completed their participation in the intervention and control conditions. Each condition consisted of four sessions, lasting 1 h per session for a duration of 4 weeks. The intervention and control conditions were delivered by a near-peer lay provider to groups of approximately 8–15 students. Participants will not participate in the intervention or control condition again as part of this study but instead will complete follow-up measures to assess the long-term effects of these interventions. These interventions are further detailed in the intervention descriptions of our previous three RCTs [15, 20, 21]. Each condition consisted of an equal dose of total intervention time: four 1-h weekly sessions that focused on teaching and reinforcing the knowledge and application of the active ingredient of the condition. Each single-element intervention (i.e., growth only, gratitude only, or values only intervention) included the elements related to this one element in the combined Shamiri condition, along with additional related activities to teach and practice the same principles. Sample intervention protocols can be found in the supplementary materials for a previous article on Shamiri [21]. The general format for each intervention was as follows:In session 1, participants completed baseline measures, were introduced to the guidelines for the group and completed group activities to introduce themselves. They learned through educational discussions and simple, fun activities about the scientific literature of their assigned intervention and how the intervention might help them in their life. Session 1 typically ended with a group discussion about the active ingredient.In session 2, participants heard stories and anecdotes related to the active ingredient of their assigned condition. Participants also completed a writing exercise to digest information from this session. Mid-point measures were collected at the end of session 2.In session 3, participants completed evidence-based exercises related to the active ingredient which taught participants how to apply what they have learned to solve real-life problems. Participants were also typically asked to apply these techniques to a hypothetical scenario.Session 4 summarized what participants had learned about the active ingredient through discussion and group activities. Participants completed endpoint measures at the end of this session. The active ingredients which participants were previously randomized to are described below:
